### Economic evaluation

Whilst it will not be possible to conduct a full economic evaluation, we will investigate the feasibility of undertaking a full economic evaluation. We will ask participants to complete a Mother and Baby Questionaire, to examine patterns of health and social care service use. Participants will also be asked to complete the EQ-5D-5L. We will identify the main cost drivers, by looking at the frequency and value of resources used, as well as any differences between arms. For economic outcomes, we will assess completeness and floor/ceiling effects in utilities at each time point with a view to assessing the suitability of the measure for a cost/QALY measure.

### Progression criteria

Our criteria for determining the success of the feasibility study are recruitment of at least 36 participants (75% of the target sample); uptake of ESGs by at least 75% of participants in the active arm of the trial and completion of 4-month follow-up assessments by 75% of the target sample. To determine the feasibility of calculating a cost analysis of health economics, we will record completion rates for the cost data and analyse them to determine what the cost-drivers are likely to be if proceeding to a full clinical trial.

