### Outcomes

#### Feasibility outcomes

The main aim of this study is to demonstrate the feasibility of conducting a trial to evaluate the intervention, including the feasibility and acceptability of randomising the intervention during the perinatal period and the feasibility of outcome measure collection.

Feasibility of recruitment will be assessed by exploring:The appropriateness of the eligibility criteria, as measured by the number of those referred to the trial over the study period, who meet the eligibility criteria.The success of recruitment, as measured by the number of eligible patients who consent to participate in the trial over the study period, and the number of patients who decline to participate.Retention rates, as measured by the number of participants who consent to participate that remain in the trial by 4-month follow-up.

Feasibility of the assessment battery will be assessed by measuring:The number/proportion of participants with complete baseline data over the study periodThe number/proportion of participants with complete follow-up data at 4 months follow-up.

Feasibility of the intervention will be assessed by measuring:The number/proportion of participants attending all 12 sessions of treatment during the treatment phase of the studyThe number/proportion of participants attending at least 9 sessions of treatment during the treatment phase of the studyThe number/proportion of participants retained at the end of each module of treatment.

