### Sample size

In keeping with recommendations for feasibility studies [32], we have not based plans for sample size on a power calculation. A pragmatic sample size of 48 will allow us to estimate, with a desirable degree of precision, the rate of recruitment and retention in a future phase III trial. In 2018, in the selected catchment areas covered by Bristol and London, there were a total of 24,697 live births (www.ons.gov.uk). Assuming a community prevalence of BPD of 2% [33], across the 2 centres, 494 women with BPD could have been eligible for recruitment. Our recruitment target of 48 women from a pool of 494 (9.7%) is a low recruitment target, but we have been cautious as people diagnosed with BPD can be harder to recruit to studies [34]. Notwithstanding, our collaborators in perinatal services, the third sector and our advisors with lived experience of personality disorder have all encouraged us to undertake this study. We therefore think that there will be significant interest in the research and that the recruitment rate will be higher. Assuming a conservative recruitment estimate of 9.7%, a sample size of 48, will give us a 95% confidence interval for recruitment of between 7.3% and 12.7%. The trial aims to recruit 48 participants over 12 months from 2 perinatal mental health services at 2 trial centres, with a target of approximately 4 participants randomised per month.

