### Assignment of interventions

After consenting to participation and completing screening assessments, eligible individuals will be randomly allocated, on a 1:1 ratio, to either ESGs + TAU or to TAU. The randomisation sequence will be generated by the Research Electronic Data Capture Service (REDCap) at the University of Bristol (https://brtcclinical.bris.ac.uk/redcap/). Randomisation will be stratified by centre. Appropriate staff at all sites, as delegated by the PI, will be provided with log-in details for the secure online randomisation system. Throughout the study, the randomisation list will be encrypted and held with the Trial Coordinating Office to ensure that the study researchers remain blinded to treatment allocation. At the end of the study, the randomisation list will be unencrypted and placed in the Trial Master File.

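### The 4-month follow-up criterion amounts to 36 completers however many women are randomised, so below the target of 48 it mixes recruitment with retention

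*Protocol article*

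**What the plan says.** The Progression criteria section of the protocol article gives three conditions for success, joined by 'and':

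1. Recruitment: "recruitment of at least 36 participants (75% of the target sample", closing the bracket there.
2. Uptake: "uptake of ESGs by at least 75% of participants in the active arm of the trial".
3. Follow-up: "completion of 4-month follow-up assessments by 75% of the target sample".

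The target comes from the Sample size section: "The trial aims to recruit 48 participants over 12 months from 2 perinatal mental health services at 2 trial centres". That section also says "we have not based plans for sample size on a power calculation" and calls the figure of 48 pragmatic.

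Follow-up appears in two other places, both descriptive. The Feasibility outcomes section measures retention as "the number of participants who consent to participate that remain in the trial by 4-month follow-up". The Data analysis section reports the proportion of participants completing follow-up, with a 95% confidence interval. Neither uses the target sample as a denominator.

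**The concern.** Criteria 1 and 3 use the same phrase, and criterion 1 gives its value as 36. Criterion 3 is therefore a fixed count of completers, not a retention rate. Criterion 1 tolerates a shortfall of up to a quarter of the target. Criterion 3 then charges that shortfall again, as if it were loss to follow-up. Criterion 2 does not have this problem, because its denominator is the women actually in the active arm.

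These criteria are the pre-specified basis for judging whether a definitive trial is feasible. A trial that recruits somewhat below 48 and follows up nearly everyone could be labelled unsuccessful on follow-up. Alternatively, the denominator could be reinterpreted once the numbers are known, which would undo the point of fixing the criterion in advance.

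**Working it through.** **Inputs from the protocol article.** Target 48 (Sample size). Recruitment threshold 36, glossed as 75% of target (Progression criteria). Follow-up threshold 75% of target (Progression criteria). Recruited and randomised women are treated as the same number N; the Sample size section does the same when it expresses the target as about 4 randomised a month over 12 months (4 × 12 = 48).

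**Input assumed.** True retention at 4 months of 80%, 85%, 90% or 95%. The protocol gives no expected value.

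**Step 1: reproduce the stated figure.** 0.75 × 48 = 36. The protocol's own arithmetic is right.

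**Step 2: apply the same phrase to follow-up.** Completers required = 0.75 × 48 = 36, with no dependence on N.

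**Step 3: retention required.** This is 36/N. The alternative with randomised women as denominator requires 0.75 × N, rounded up.

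| N | Completers needed, as written | Retention needed (36/N) | Completers needed, 75% of randomised |
|---|---|---|---|
| 36 | 36 | 100% | 27 |
| 40 | 36 | 90% | 30 |
| 44 | 36 | 82% | 33 |
| 48 | 36 | 75% | 36 |

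With 36 women, one loss gives 35/36 = 97.2% retention and fails the criterion. The two rules coincide at 48. They also coincide at 47, where 0.75 × 47 = 35.25 rounds up to 36. The practical difference therefore lies at 36 to 46 women.

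**Step 4: redundancy.** Completers cannot exceed recruits. Meeting criterion 3 (36 completers) already implies at least 36 recruited, so criterion 1 can never be the condition that fails alone.

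**Step 5: chance of meeting criterion 3.** Exact binomial, P(X ≥ k) with X ~ Bin(N, p), k = 36 as written and k = 0.75N (rounded up) for the alternative. Women are assumed to complete independently with the same probability p.

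| N | Rule | p = 80% | p = 85% | p = 90% | p = 95% |
|---|---|---|---|---|---|
| 36 | as written | 0.0003 | 0.003 | 0.02 | 0.16 |
| 36 | 75% of randomised | 0.83 | 0.96 | 0.998 | 1.00 |
| 40 | as written | 0.08 | 0.26 | 0.63 | 0.95 |
| 40 | 75% of randomised | 0.84 | 0.97 | 0.998 | 1.00 |
| 44 | as written | 0.47 | 0.79 | 0.97 | 1.00 |
| 44 | 75% of randomised | 0.85 | 0.97 | 0.999 | 1.00 |
| 48 | both | 0.85 | 0.98 | 0.999 | 1.00 |

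At N = 36 the as-written figure is simply p to the power 36, for example 0.95^36 = 0.16.

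**The case against.** **Loose wording.** The uptake criterion and the Data analysis section both use actual participants as the denominator, so the authors may have meant 75% of the women recruited. That is plausible as intent. But the sentence itself fixes the phrase at 36, and nothing elsewhere corrects it. If that was the intent, the sentence is misstated and needs the same correction.

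**A deliberate floor.** A minimum number of completers can be a legitimate feasibility threshold. Here it would leave criterion 1 with no work to do, and the protocol gives no reason for such a floor.

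**Limited reach.** This objection stands. At 48 women the criterion is an ordinary 75% retention rule, and at 44 the requirement of 82% is not extreme. The Sample size section also expects strong interest in the study. Against that, it warns that people with this diagnosis can be harder to recruit, and numbers below 48 are exactly what criterion 1 was written to accept.

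**Stronger readings that the protocol does not support.** A reader might infer that missing the criterion stops the programme. The section describes criteria for success and states no automatic stop. Retention will also be reported as a proportion with a confidence interval, and acceptability will be explored in interviews, so good retention would remain visible. A reader might also infer that the retention outcome among consenting women contradicts the progression criterion. It does not: it is a descriptive measure, and a rate among those who consent is legitimate.

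**Conclusion.** The point holds for recruitment below target. As written, the follow-up criterion is a count of 36 completers, so it combines recruitment and retention in one number and makes the recruitment criterion redundant. The required retention rises from 75% at 48 women to 100% at 36; this follows from the protocol's own figures and needs no assumption. The pass probabilities do rest on assumed retention and on independent completion. At 36 women, though, the conclusion is the same across the whole range: at most 0.16 as written, and at least 0.83 with a randomised denominator. The consequence is a possible mislabelling of a well-retained trial. No treatment estimate is affected, and there is no effect at 48. The fault lies in the denominator, not in any calculation.

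**What to change.** Restate the third criterion in the Progression criteria section as completion of the 4-month follow-up assessment by at least 75% of randomised participants, which means 27 of 36 up to 36 of 48. Settle this before the follow-up results are known. The descriptive retention outcome in the Feasibility outcomes section needs no change. The cost is one sentence, with no additional data or participants.

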### Ethics

Approval for the study has been given by Camden & Kings Cross Research Ethics Committee (Reference 21/LO/0833). The trial will be conducted in compliance with the principles of the Declaration of Helsinki, the principles of Good Clinical Practice, and all of the applicable regulatory requirements (UK data protection laws (meaning the Data Protection Act 1998 until 24 May 2018, and the European Union General Data Protection Regulation (GDPR) and applicable UK legislation that enshrines GDPR into UK law).

As part of the informed consent process, participants will be advised and provided guidance about confidentiality and the limits to it. Significant risk of future harm to self or their baby will be disclosed to their healthcare professional.

The trial may be prematurely discontinued by the Sponsor or Chief Investigator on the basis of new safety information or for other reasons given by the Trial Steering Committee, regulatory authority or ethics committee concerned. The trial may also be prematurely discontinued due to lack of recruitment or upon advice from the Trial Steering Committee. If the study is prematurely discontinued, active participants will be informed and no further participant data will be collected.

## Discussion

Women with BPD experience unique challenges during the perinatal period and currently there is a dearth of evidence about how best to help them during this important phase of the life course. This study will test the feasibility of using a randomised trial to examine the clinical and cost effectiveness of perinatal Emotional Skills Groups for women with BPD. Pre-trial non-randomised pilot work [31] has shown that perinatal ESGs are a promising intervention and if ESGs prove to be a clinically and cost-effective adjunct to usual care, a large population of vulnerable women would experience substantial health gains. Furthermore, given the inter-generational health risks associated with BPD [5, 37], enhancing the coping skills of women with BPD may also benefit the health of their children.

The trial has a number of strengths. We have adopted a pragmatic design, with broad inclusion criteria and a limited number of exclusion criteria. BPD often co-occurs with other mental health problems and we will therefore include women with BPD who have co-morbid depression, anxiety or substance use disorders. The latter category is particularly important as women with substance use problems are often excluded from BPD treatment trials. We decided to include pregnant and post-natal women in the trial for three reasons: first, the inclusion of both groups reflects the reality of perinatal mental health service delivery; second, treatment may offer benefits to women across the perinatal period; finally, prior work [17] shows that it is acceptable to run groups with both pregnant and post-natal women and that most women do not view pregnancy and the post-natal period as ‘separate’ parts of their maternity experience. The outcome domains have been carefully selected following consultation with women with lived experience of perinatal mental health services, as well as health care professionals. In addition, the collection of both qualitative and quantitative data will allow us to make a comprehensive assessment of the acceptability and feasibility of the study design.

There are also some limitations of the trial. In keeping with the approach adopted by other recent trials in the personality disorder field [38, 39], we have not included a detailed assessment of personality disorders. This is because such assessments are time-consuming to complete and this is not in keeping with the needs of a pragmatic study that will be conducted in a busy clinical setting. We will however be screening all potential participants with the SAPAS, which has good predictive validity [40–42]; these baseline data will provide useful information about the severity of personality disturbance. A further limitation is the restricted length of follow-up to 4 months. We have adopted this approach because our primary aim is to establish the feasibility of recruitment and randomisation. However, we acknowledge that BPD is a long-term condition, and a future definitive trial would benefit from having a longer-term follow-up of at least 12 months.

## Data Availability

Not applicable.

## Abbreviations

BPD: Borderline personality disorder
CORE-10: Ten-item Clinical Outcomes in Routine Evaluation Scale
CRF: Case Report Form
EQ-5D-5L: EuroQol Group 5-Dimensions 5-level
ESGs: Emotional Skills Groups
GDPR: General Data Protection Regulation
PIS: Participant Information Sheet
PSS: Parenting Stress Scale
SAPAS: Standardized Assessment of Personality-Abbreviated Scale
TAU: Treatment as usual
ZAN-BPD: Zanarini Rating Scale for Borderline Personality Disorder Self-Report Scale
SWEMWBS: Short Warwick Edinburgh Wellbeing Scale
WSAS: Work and Social Adjustment Scale
